#### Aim 2, linkage

To determine whether linkage to care is higher among residents of intervention versus control communities as measured by (a) proportion of those testing HIV positive who complete CD4 staging within 3 months of diagnosis and (b) the proportion of those eligible for treatment who initiate ART within 3 months of CD4 staging.

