### Study measures

#### Primary exposure

Residence in an intervention or control community is the primary predictor variable for all analyses. Community of residence will be determined using the HDSS data. Household and vital events data are updated annually and include births, in- and out-migrations and deaths. Although few individuals are expected to move within the study area over the course of the study, for those who do move, exposure will be determined dynamically over the course of the study such that individuals will be considered exposed if they were resident in an intervention community in the time period immediately prior to the outcome. Table 2 summarizes the quantitative data elements that include exposures, outcomes, mediators, and social and demographic co-variates.

**Table 2 Tab2:** Summary of quantitative data elements

Domain	Instrument/measure	Data source and frequency
Primary exposure		
Village	Village of residence (binary; intervention vs. control village)	HDSS-annual
Primary outcomes		
Testing uptake (aim 1)	Binary: tested/untested past 12 months, among HIV-negative or unknown status residents	Electronic health facility records-ongoing
	Binary: known HIV status–either confirmed positive or tested within the last 12 months	Electronic health facility records-ongoing
Linkage to HIV care (aim 2)	Binary: received baseline CD4 results and evidence of follow-up care (additional CD4, viral load, or treatment initiation) within 3 months of testing HIV positive	Electronic health facility records-ongoing
	Binary: treatment initiation within 3 months of positive diagnosis among those eligible for ART	Electronic health facility records-ongoing
Retention in HIV care (aim 3)	Binary: HIV patients on or initiating ART who have no more than a 90-day gap in medication received in the 12-month period (no defaulting).	Electronic health facility records-ongoing
	Binary: HIV patients not ART eligible^a^ who have a repeat CD4 test 6–12 months after initial CD4	Electronic health facility records-ongoing
Meditator/mechanism		
Community mobilization	Six domains of community mobilization measure [53]	Population-based surveys (years 1 and 5)
Covariates		
Demographics	Age, SES, gender, migration status	HDSS-annual
Social norms	Stigma [81]; gender norms [41]; community support for HIV testing and treatment [53]	Population-based surveys (years 1 and 5)
Secondary outcomes		

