Testing (aim 1)	Median CD4 of people initiating ART (to explore earlier testing, entry into care)	Electronic health facility records-ongoing
Re-engagement in care (aims 2 and 3)	Patients out of care (not retained) who are re-engaged in care (have a CD4 test/initiate or re-initiate treatment).	Electronic health facility records-ongoing
Viral suppression	Proportion of residents with viral load <400 copies/ml	Electronic health facility records-ongoing
Secondary exposure		
Intervention coverage	Reported exposure to intervention events	Population-based surveys (years 1 and 5)

^a^Prior to September 2016, patients were considered ART eligible with one or more of the following criteria: pregnancy, CD4 count lower than 500 cells/mm [3], active tuberculosis, WHO stage 3 or 4, or initiation of ART per clinician discretion. Universal treatment was planned to be instituted in September 2016; therefore, all HIV-positive individuals will be considered treatment eligible after this date; the pre-ART definition will only apply to the period prior to implementation of the universal treatment guidelines

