### Power

Minimum detectable differences were calculated according to the methods for proportions in cluster randomized trials proposed by Hayes and Moulton [54], yielding conservative effect size estimates based on clustering by villages. Based on the HDSS data, there are approximately 30,000 adults 18–49 in the study area. We assumed an HIV prevalence of 33% in the adult target population (18–49-year old) [51]. If we conservatively estimate that testing is constant at 35% of the population, at least a third of those tested each year were not tested previously in the study period, and that test positivity is 15% (again a conservative estimate), 449 cases of HIV would be newly identified each year. We further assumed that approximately 50% of individuals who present for CD4 staging would be eligible for HIV treatment under 2014 guidelines. Approximately 6000 individuals were known to be on treatment at clinics in this area in 2014. Our survey data from 2012 suggests that HIV testing in this region exhibits an intra-class correlation of 0.014. In adjustments of power calculations for clustering of outcomes by village, we conservatively assumed an intra-class correlation of 0.05. Table 3 includes outcome estimates for the control proportions based on current literature [18, 26, 27, 68, 79], and the target (intervention) proportions with the minimum increase in proportions that would be detectable as a statistically significant change at alpha of 0.05 and power of 0.80, given the above assumptions. In 2016 (1 year into data collection), the South African government announced universal HIV treatment. This should increase our sample size to assess initiating ART (aim 2) and retention in care (aim 3) in the second and third years of the study.

**Table 3 Tab3:** Power calculations–minimum detectable effects

Outcomes: proportion of population	Current estimate	Intervention group target	Minimum detectable difference (proportion)
Testing; tested in past 12 months	35%	60%	19%
Linkage; undergoing CD4 staging within 3 months of positive test	65%	85%	18%
Linkage; eligible for ART who initiate treatment within 3 months	60%	80%	19%
Retention; HIV positive who remain in care at 12 months	50%	70%	19%

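### Before September 2016 the only printed definition of ART eligibility includes starting ART; if it governs the primary initiation outcome, that denominator depends partly on the outcome

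*Protocol article*

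**What the plan says.** Table 2 lists as a primary linkage outcome "Binary: treatment initiation within 3 months of positive diagnosis among those eligible for ART". Aim 2(b) gives the same quantity with a different clock: "the proportion of those eligible for treatment who initiate ART within 3 months of CD4 staging". Neither place says who is eligible.

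Footnote a to Table 2 does. For the period before September 2016, "patients were considered ART eligible with one or more of the following criteria": pregnancy, a CD4 count below 500, active tuberculosis, then "WHO stage 3 or 4, or initiation of ART per clinician discretion". After that date "all HIV-positive individuals will be considered treatment eligible after this date", and the footnote adds that "the pre-ART definition will only apply to the period prior to implementation of the universal treatment guidelines".

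The marker for the footnote is printed only on the retention row for HIV patients who are not ART eligible, that is, those "who have a repeat CD4 test 6–12 months after initial CD4". It is not printed on the initiation row.

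**The concern.** Four of the five criteria describe the patient independently of whether treatment is started. The fifth is the start of treatment itself. Take two patients with the same CD4 count, neither meeting any of the other four criteria. The one who starts ART at the clinician's discretion becomes eligible and is counted. The one who does not start is left out. If this definition feeds the initiation outcome, membership of its denominator is decided partly by the event being measured.

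Two consequences follow for the arm comparison. If mobilization leads more such patients to start ART, the measured proportion in intervention villages can move even though initiation among the otherwise eligible has not changed. If discretionary starts are equally common in both arms, they add the same number of successes to each and pull the two proportions together.

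The retention row that carries the marker is touched as well. Patients who start by discretion leave the not-eligible denominator after the fact, and those who remain may be less engaged with care.

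**Working it through.** **Inputs from the protocol article.**
- Share eligible: "approximately 50% of individuals who present for CD4 staging would be eligible for HIV treatment under 2014 guidelines" (Power).
- 449 new diagnoses a year, ICC 0.05, alpha 0.05, power 0.80 (Power).
- ART initiation 60% in control, target 80%, minimum detectable difference 19 points (Table 3).
- 8 and 7 villages (Specific aims).
- Intervention from 1 August 2015 to July 2018 (Trial status): 36 months, of which 13 fall before September 2016.

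**Assumed, because the article gives no figure.** Discretionary-start rates; eligible shares other than 50%; even accrual; 60% initiation in both arms throughout.

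**The plan's own figure.** The Hayes–Moulton formula for proportions is c = 1 + (1.96 + 0.84)² × [p0(1−p0) + p1(1−p1)] × [1 + (m−1)ρ]/m ÷ (p1−p0)². Cluster size is not stated; three years of accrual gives m = 449 × 0.5 × 3 / 15 = 44.9. With p0 = 0.60 and ρ = 0.05, the detectable difference is 19.4 points for c = 7 villages per arm, 18.8 for c = 7.47 (harmonic mean) and 18.7 for c = 7.5. All round to the stated 19, so that figure is used as the yardstick.

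**Effect of the clause in the affected months.** Let e be the share meeting one of the other four criteria, p their 3-month initiation, and d the share of the remaining patients who start by discretion within 3 months. The measured proportion is

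[e·p + (1−e)·d] / [e + (1−e)·d].

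With e = 0.50 and p = 0.60:
- d = 10%: (0.30 + 0.05)/(0.50 + 0.05) = 63.6%
- d = 30%: (0.30 + 0.15)/(0.50 + 0.15) = 69.2%

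The gap is 5.6 points, although initiation among the otherwise eligible is 60% in both arms.

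**Pooled over 36 months.** With everyone eligible in the last 23 months, the proportion is [13(e·p + (1−e)d) + 23 × 0.6] / [13(e + (1−e)d) + 23].
- d = 10%: (4.55 + 13.8)/(7.15 + 23) = 60.9%
- d = 30%: (5.85 + 13.8)/(8.45 + 23) = 62.5%

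The gap is 1.6 points, or 1.6/19, about 8–9% of the detectable difference. Weighting months rather than patients equally gives 5.6 × 13/36 = 2.0 points.

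| Otherwise eligible (e) | d, control v intervention | Gap, affected months | Gap, pooled |
|---|---|---|---|
| 50% | 0% v 10% | 3.6 | 0.9 |
| 50% | 5% v 20% | 4.8 | 1.3 |
| 50% | 10% v 30% | 5.6 | 1.6 |
| 70% | 0% v 10% | 1.6 | 0.5 |
| 70% | 5% v 20% | 2.3 | 0.7 |
| 70% | 10% v 30% | 2.9 | 0.9 |
| 85% | 10% v 30% | 1.3 | 0.4 |

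**Equal discretionary starts.** With e = 0.50 and d = 10% in both arms, a true 60% v 80% is measured as 63.6% v (0.40 + 0.05)/0.55 = 81.8%, so 20.0 points become 18.2. With d = 20% it becomes 16.7. Pooled over 36 months, the 10% case gives 60.9% v (5.85 + 18.4)/30.15 = 80.4%, or 19.6 points.

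**Late starts.** The clause carries no time limit. If 10% of the remaining patients start by discretion within 3 months and another 10% later (assumed), the measured proportion is 0.35/(0.50 + 0.10) = 58.3%, below the 60% among the otherwise eligible. The direction is therefore not fixed.

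**The case against.** The strongest reply is that the footnote belongs to another row. Its marker sits on pre-ART retention, where setting aside people who have started treatment is understandable, because Table 2 has a separate retention row for patients on or initiating ART. This stands as a limit: use for the initiation row is inferred. The inference is strong, since no other patient-level definition is printed and the Power section expects universal treatment to enlarge the sample for ART initiation under Aim 2, so one eligibility rule appears to serve both.

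Second, both arms use the same clinics, and the Discussion says clinic-directed activities run in all study facilities. That limits differences in clinician behaviour. It does not remove differences in patient demand, which the intervention sets out to raise, but a threefold difference in discretionary starts is purely an assumption.

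Third, extra starts caused by mobilization would be a real effect on treatment uptake. That is fair. The difficulty is that they are measured on a denominator that shifts with them.

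A reader might go further and infer that discretionary patients contribute only successes, that the proportion must be inflated in both arms, or that the clause can produce about 30% of the detectable difference (5.6 of 19 points). The article does not support these readings. Starts after 3 months count as failures. The 5.6 points rest on assumed rates and apply to the early period only, whereas the Analysis section plans a time-averaged comparison. At e = 0.50, a false 19-point gap in the affected months, from no discretionary starts in control, would need about 90% of the remaining intervention patients to start by discretion.

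**Conclusion.** The concern holds in limited form, at moderate severity. The only eligibility definition in the article includes the outcome event for the period before September 2016. If it governs the initiation outcome, the denominator is conditioned on that outcome for about 13 of 36 intervention months, after which the article's own rule removes the problem.

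A false arm difference requires discretionary starts to differ by arm. Under the assumptions tabulated, it is about 1 to 6 points in the affected months and about 0.4 to 1.6 points pooled. With equal rates, the result is modest dilution of a true effect. The trial's conclusion is unlikely to turn on this clause alone, but the definition should not be left as printed.

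**What to change.** These changes concern the analysis only and leave patient care untouched.

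- For the initiation outcome, define the denominator before September 2016 by the four listed criteria that do not depend on starting ART (pregnancy, CD4 count, tuberculosis, WHO stage), and say explicitly which eligibility definition applies to that row.
- Report discretionary starts separately, by arm, as a proportion of all newly diagnosed patients.
- For the not-eligible retention outcome, add a sensitivity analysis that keeps in the denominator patients who later started ART only by discretion.

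Settle this before outcome data by arm are examined. The cost is one clause in the footnote, a filter in the analysis code and a somewhat smaller early denominator. With e = 0.50, discretionary starts of 10% or 30% would mean losing 0.05/0.55 = 9% or 0.15/0.65 = 23% of the denominator before September 2016, which is 0.65/30.15 = 2% or 1.95/31.45 = 6% of the pooled one.

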#### Primary outcomes

For each aim, the primary source of data for outcomes is the electronic health facility data linked to the HDSS. An electronic record will be created for every resident of the 15 study villages captured in the population database; with this approach, we will treat the entire eligible (18–49-year old) population in the area as an open cohort, assuming no clinic visits were made if none were captured for a given individual. Study outcomes include HIV testing uptake in the past 12 months among residents of negative or unknown status (aim 1); linkage to HIV care, or having returned to the clinic following diagnosis for ART initiation or follow-up care (aim 2); and retention in care, defined as remaining on ART with no more than a 90-day gap in coverage over a 12-month period (aim 3).

#### Mediators: community mobilization

Quantitative measures of CM will be collected in the two community surveys; CM is comprised of six hypothesized domains, outlined in Table 1. Questions regarding a *shared concern* about HIV/AIDS are designed to capture whether members of the community define HIV testing and care as important, problematic, and mutable issues, and whether they believe they can work together to address HIV. The scale for *critical consciousness* is designed to capture whether members of the community are undergoing processes of critical reflection and dialogue about their circumstances and ways to improve their lot. Questions about *leadership* capture leadership capacity, diversity, responsiveness, accessibility, and support of collective decision making. Questions regarding *organizations and networks* are designed to capture the existence and influence of community-based organizations, groups, and networks that can serve as a resource in mobilizing—both for exchange and diffusion of ideas and as a structure that can be utilized for community organizing. Questions regarding *collective action* are designed to capture the presence, breadth, and quantity of collective activities in the villages aimed at social change. Finally, questions about *social cohesion* capture the level of working trust in a community. Scales performed extremely well for all six CM domains in our 2012 survey [53].

### Analysis

One-way frequency tables for all variables and measures of central tendency and variability for continuous variables will be generated to perform range checks, quantify the amount of missing data, and yield valuable descriptive findings that will further characterize the care cascade in the study population. These analyses will also be stratified by randomization group (i.e., intervention versus control) using cluster-based two-group comparison methods (e.g., Rao-Scott chi-square) to check the equality of intervention and control group covariates at baseline. If the intervention and control groups are found to differ significantly at baseline on one or more covariates (e.g., gender; mean age of village residents), we will use methods based on the Rubin causal model (e.g., propensity scores, targeted maximum likelihood estimation, double-robust estimation) [60] to obtain the desired marginal effect estimates under the counterfactual assumption of balanced groups [61–65]. We will assess and document the amount of missing data from health facility systems and community surveys. In the unlikely event that a variable has >5% of missing data, we will address incomplete data via either inverse probability of censoring weights (IPCW) or use multiple imputation (MI) [66], as it makes the relatively mild assumption that incomplete data arise from a conditionally random (MAR) mechanism rather than the completely random process (MCAR) assumed by ad hoc methods such as list-wise data deletion [67]. For MI, auxiliary variables will inform multiple imputations to increase the likelihood of meeting the MAR assumption [68, 69].

We hypothesize that following the intervention, for the intervention community relative to the control community residents:The odds of HIV testing will be higher (specific aim 1);The odds of linkage to care will be higher (among those HIV-infected; specific aim 2);The odds of retention in care will be higher (among those HIV-infected; specific aim 3); andThe community means of the six domains of community mobilization will be higher and associated with individual level outcomes (specific aim 4).

Primary analyses will follow an intent-to-treat (ITT) approach and will be unadjusted except for intervention group, and, for longitudinal analyses, time, and the group-by-time interaction. Individual will be the unit of analysis. Our principal interest is to estimate the marginal or population-average effect of the intervention on each outcome rather than the effect for a hypothetical average subject [70]. Moreover, within-subject correlations among outcomes are considered nuisance parameters rather than quantities of interest to be modeled explicitly. Accordingly, generalized estimating equations (GEE) will be used to perform the proposed primary longitudinal analyses, including planned time-averaged comparisons of post-baseline measurements across the intervention and control arms to test primary hypotheses 1–3 listed above. Alpha will be set at .05 for these planned comparisons of each separate outcome. Any additional post-hoc comparisons (e.g., paired comparisons of the control and intervention arms at each time point) will maintain a nominal alpha level of .05 through the use of simulation-based stepdown multiple comparison methods [71]. GEE accounts for correlation of repeated measurements from the same research participant via computation of a working correlation matrix and yields the desired marginal population-average effect estimates [72]. Village ID will be included as a nested fixed effect or via alternating logistic regression (ALR) to account for clustering of persons nested within villages. GEE estimates are consistent even if the correlation structure is mis-specified, though GEE’s statistical efficiency improves as the working correlation structure more closely approximates the actual correlation structure [73]. Thus, several suitable working correlation structures will be considered (e.g., unstructured, AR(1), exchangeable) [74]. The QIC or a similar statistic will be used to select the final working correlation structure [75]. Robust Huber-White “sandwich” standard errors will be used to obtain correct inferences even if the chosen correlation structure remains slightly mis-specified.

For hypothesis 4, cross-sectional population data will be collected through representative community surveys. Summary measures of the CM domains before and after the intervention for each village will be calculated from this population representative sample. GEE will be used to model the effects of the pre-post differences in village-level CM domains on individual residents’ HIV testing, and, for HIV-positive individuals, linkage and retention to care using the same overall modeling approach as outlined above. To examine the relative importance of each of the six CM domains, initial models will include the pre-post change scores for each of the six domains in a single model. Subsequent analyses will isolate the marginal effects of each domain via G-computation or other substitution-based estimation strategy [60, 76].

Secondary analyses will extend GEE models to incorporate additional covariates of interest drawn from the HDSS data (e.g., age; gender) and examine their interactions with intervention assignment to ascertain statistical moderation. Secondary analyses will also evaluate whether the pre-intervention/post-intervention village-level difference in the six community mobilization measures mediate the relationships between intervention village residence and the primary outcomes. Statistical mediation will be assessed using the causal inference-based approach of Valeri and VanderWeele, which yields optimal estimates of indirect effects in the presence of binary outcomes and moderator-mediator interactions [77]. M*plus* will be used to implement these mediation analyses because it allows for causal mediation assessment incorporating robust standard errors to address clustering of individuals within villages [78]. Significant indirect and total effects of the intervention on testing, linkage, and retention accompanied by non-significant direct effects will signify mediation in this context.

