### Community randomization

Communities involved previously in community mobilizing activities (*n* = 12), those not yet fully enumerated in 2014 (*n* = 3), and with fewer than 500 permanent residents (*n* = 1) were not eligible to participate, leaving 15 communities to randomize. In order to achieve a balance among villages on the key covariates at baseline, a restricted or balanced randomization approach [54] was used, taking into account population size, distance to closest health facility, average levels of SES based on household assets [55], temporary migration, female-headed households, and baseline community mobilization scores [53], collected as part of a survey in 2014. Cluster allocation cannot be concealed as CM events and activities are held in public spaces. Further, village leaders were consulted about the trial, consented for their villages to participate, and were present for the allocation. A randomization event was carried out with community representatives. A biostatistician unfamiliar with the area and the villages generated 50 different grouped combinations of intervention and control villages, and these combinations were printed on strips. The assignment was revealed by asking a community volunteer to pick the winning randomization scheme out of a bucket containing all 50 possibilities. The program was then launched in the presence of local leaders and community members.

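### A baseline significance test can call in a second estimator for the same marginal effect without saying which result is primary, and no analysis commits to the factors that restricted the randomisation

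*Protocol article*

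**What the plan says.** Three statements in the protocol article bear on this point.

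- **Analysis, first paragraph.** The arms are compared at baseline "using cluster-based two-group comparison methods (e.g., Rao-Scott chi-square) to check the equality of intervention and control group covariates at baseline". The next sentence begins "If the intervention and control groups are found to differ significantly at baseline on one or more covariates" and continues "we will use methods based on the Rubin causal model" (propensity scores, targeted maximum likelihood and double-robust estimation are the examples), "to obtain the desired marginal effect estimates under the counterfactual assumption of balanced groups". No test level is given, and the covariates are named only by example (gender, mean age).
- **Analysis, paragraph on primary analyses.** "Primary analyses will follow an intent-to-treat (ITT) approach and will be unadjusted except for intervention group", with time and the group-by-time interaction added for longitudinal models. GEE is chosen because it "yields the desired marginal population-average effect estimates".
- **Community randomization.** "a restricted or balanced randomization approach [54] was used, taking into account population size, distance to closest health facility", together with SES, temporary migration, female-headed households and baseline mobilisation scores. Fifty allocations were generated and one was drawn.

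The secondary analyses extend the GEE models with HDSS covariates, again with age and gender as the examples. They do not mention the analysis that the baseline test would call in.

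**The concern.** There are two linked problems.

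1. **Two estimators, one target.** Both statements in the Analysis section aim at the desired marginal effect. If the baseline test is significant, the text says that the causal-model methods will be used. The text on primary analyses says without condition that they are unadjusted. Nothing ranks the two results, so a reader cannot tell which one tests hypotheses 1–3 if they disagree.

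2. **The wrong covariates are favoured.** After randomisation, a significant baseline difference is chance. With 15 villages, significance says little about whether an imbalance matters for the outcome. Variables balanced by design will seldom be significant, so the rule steers adjustment away from the factors the investigators thought important enough to restrict on. A propensity model for village assignment also has only 15 assigned units, however many residents are analysed. An unadjusted standard error takes no credit for the balance achieved, so the test is conservative if those factors are prognostic. Power is then lost in a trial limited by its number of villages.

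**Working it through.** The plan gives no figure on this point to reproduce. The checks concern how often the trigger fires and what leaving out the restriction factors costs.

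**Inputs from the article:** 8 intervention and 7 control villages; six restriction factors; 50 allocations; alpha 0.05 per outcome (two-sided assumed); about 30,000 adults; 449 new cases a year; about 50% eligible for treatment; ICC 0.05. Table 2 lists age, SES, gender and migration status, plus three norm measures (stigma, gender norms, community support).

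**Step 1. How often the trigger fires by chance.** For k independent tests at 0.05, P(at least one significant) = 1 − 0.95^k.
- Age and gender, not restricted on: 1 − 0.95² = 9.8%.
- With the three norm measures: 1 − 0.95⁵ = 22.6%.

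A cluster-level simulation (allocation drawn from the 50 best-balanced of the 6,435 possible 8:7 splits, six restricted and two unrestricted covariates, 4,000 runs per setting) agrees. The trigger fired in about 10% of trials, always through the two unrestricted covariates.

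**Step 2. Whether the trigger damages the error rate.** In that simulation all eight covariates together explain a share R² of village-level outcome variance. Regression adjustment of village summaries stands in for the causal-model methods.

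| Type I error | R² = 0 | R² = 0.3 | R² = 0.6 |
|---|---|---|---|
| Unadjusted | 4.9% | 2.6% | 1.1% |
| Adjusted only if triggered | 5.0% | 2.4% | 1.1% |
| Whichever of the two is significant | 5.2% | 2.8% | 1.3% |

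The trigger hardly moves the error. The fall below 5% comes from an unadjusted test after restricted allocation.

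**Step 3. Why the unadjusted test is conservative.** If restriction balances the prognostic factors almost exactly, the true variance of the arm difference is about (1 − R²) times what the unadjusted standard error assumes. The 5% critical value, t(13) = 2.160, then acts like 2.160/√(1 − R²).
- R² = 0.2: 2.160/√0.8 = 2.415, two-sided tail of t(13) = 3.1%.
- R² = 0.4: 2.160/√0.6 = 2.789, two-sided tail of t(13) = 1.5%.

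**Step 4. What prespecified adjustment would recover.** Same allocation scheme, with two of the six restriction factors prognostic and a village effect of 1.5 SD.

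| Assumed R² | Type I, unadjusted | Type I, two factors | Power, unadjusted | Power, two factors |
|---|---|---|---|---|
| 0 | 5.2% | 5.4% | 77% | 75% |
| 0.2 | 3.3% | 5.0% | 77% | 83% |
| 0.4 | 1.4% | 4.9% | 79% | 91% |

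Repeat runs moved type I error by about half a point and power by up to two points.

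**Step 5. Where the gain is smaller.** With m people per village, the between-village share of the variance of a village proportion is ICC/[ICC + (1 − ICC)/m].
- Testing, m = 30,000/15 = 2,000: 0.05/(0.05 + 0.0005) = 99%.
- CD4 staging, one year's cases, m = 449/15 ≈ 30: 0.05/(0.05 + 0.0317) = 61%.
- ART initiation, half of those, m ≈ 15: 0.05/(0.05 + 0.0633) = 44%.

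Village covariates act mainly on the between-village part, so linkage gains less than testing.

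**The case against.** The best defence is that the primary analysis is stated without condition, while the trigger sentence follows descriptive tables and never uses the word primary. On that reading the triggered analysis is supportive, the shared phrase about the desired marginal effect shows only a common estimand, and a fuller plan may supply the label. This is a possible reading, and a sensitivity label would end the conflict. But the article says the methods will be used, names the same target, and does not list the analysis among the secondary ones. Two stated rules meet and neither yields.

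Several stronger readings are tempting and should be resisted.

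- **That a data-driven choice of estimator inflates false positives.** Step 2 shows no material inflation. The departure from 5% is conservative and comes from the restriction.
- **That the trigger would fire in 19% of trials (four demographics, 1 − 0.95⁴) or 49% (13 variables, 1 − 0.95¹³).** SES, migration and the six mobilisation scores overlap the factors balanced by design, which leaves about 10% and 23%.
- **That adjustment would cut the 19-point detectable difference to 15–17 points.** That rests on an assumed R², treats all variance as between villages, and ignores what restriction already gains for the unadjusted estimate.
- **That the restriction factors are excluded.** They are not committed to. SES and migration status are covariates in Table 2 and could enter.

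It also stands that a prespecified unadjusted analysis is valid, and that adjusting for many factors with 15 villages can cost what it gains. Adjustment for all six gave power of 77% against 79% unadjusted at R² = 0.3, and 89% against 80% at R² = 0.6.

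**Conclusion.** The point holds as an ambiguity in the primary analysis plus a likely loss of power. The article does not say which estimate tests hypotheses 1–3 when the baseline test is significant, which by chance would be about one trial in ten to nearly one in four, depending on how many unbalanced variables are tested. That range assumes independent tests at the 5% level.

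Separately, the six restriction factors are carried into no committed analysis. If two of them explain 20–40% of village-level outcome variance, the unadjusted test gives up about 6 to 12 points of power. If they explain nothing, adjusting costs about 2 points. The article gives no R², and the simulations assume the 50 best-balanced allocations and a test on village-level summaries in place of the planned GEE, so these sizes are indicative. The documents do not support a claim that the trial's false-positive rate is inflated by the trigger.

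**What to change.** 1. Delete the baseline-significance trigger, or state that the causal-model analysis is a sensitivity analysis whatever the baseline tests show. Baseline tables can stay as description.
2. Before outcome data by arm are analysed, prespecify one primary model adjusted for one or two restriction factors, for example distance to facility and baseline mobilisation score, with age and sex if wanted. Standardise the result to the marginal effect so that the population-average estimand is kept.
3. Report the unadjusted result as supportive.

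The cost is an amendment and some analysis work. The restriction factors were available at randomisation, and age and sex are in the HDSS. Each village-level covariate uses one of 13 degrees of freedom. Adjusting for only one or two of the six factors may leave some conservatism if the others are prognostic, and the benefit will be smaller for linkage than for testing. Because the intervention is already under way, the amendment should be dated and should state that outcomes by arm had not been analysed.
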